## 10.4 Analysis Populations

### 10.4.1 Full Analysis Population

The Full Analysis Population (FAP) includes all randomised patients with treatment groups assigned in accordance with the randomisation, regardless of the treatment actually received. Patients who were randomised but did not subsequently receive treatment are included in the Full analysis population. The analysis of data using the Full analysis population therefore follows the Intention-to-Treat principles (ITT).

### 10.4.2 Per Protocol Population

In the per protocol population, patients with important protocol deviations are excluded. Definition of important protocol deviations are given in the statistical analysis plan (SAP).

### 10.4.3 Safety Population

All enrolled patients who received treatment are subjected to the safety analysis. Patients will be evaluated with regard to the treatment actually received, meaning that patients who cross

over from the control to the experimental arm will be evaluated in the experimental arm from day 10 onwards. Details of the safety analysis are specified in the statistical analysis plan (SAP).

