26. **AE assessments:** events are documented and recorded continuously. Patients must be followed for AEs from first plasma administration up to 28 days after last plasma administration or until all drug-related toxicities have been resolved, whichever is later, or until the investigator assesses AEs as "chronic" or "stable". Each AE must be reported, indicating the worst CTC (Version 5.0) grade. If an event stops and later restarts, all occurrences must be reported. A specific procedure for definition and reporting of SAEs is described in the protocol.

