## **6.8 Cross Over**

Cross-over into the experimental arm is intended for patients randomized into the standard arm if the following criteria is met:

- Starting from day 10 after randomization
- No improvement or worsening of clinical condition

For cross-over, all inclusion / exclusion criteria (except mechanical ventilation/ECMO) must again be met as specified in Sections 5.3 and 5.4.

The actual possibility for cross-over into the experimental arm is based on discussion with the coordinating investigator on a case-by-case decision.

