**CROSS-OVER OPTION into experimental arm:**

Cross-Over starts with baseline visit and follows the primary schedule of the study as described in the trial schedule (Table 1).

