### **Safety Analysis**

The assessment of safety is based mainly on the frequency of adverse events and on the number of laboratory values that fall outside of pre-determined ranges and/or show prominent worsening from baseline during the study phase. Safety analysis is based on the safety population. Adverse events are summarized by presenting the number and percentage of patients having any adverse events or serious adverse events, and having each individual adverse event, and by determining and summarizing the maximum individual toxicity grade (over all forms of toxicity). Furthermore, the most common AEs (those occurring in at least 10% of the treatment group) are determined. Any other information collected (e.g. severity or relatedness to study drug) are summarized as appropriate. Laboratory data are summarized by presenting summary statistics of raw data and change from baseline values. Incidence rates are summarized along with two-sided Clopper-Pearson 95% confidence intervals and analyzed by (descriptive) chi-squared tests.

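### Section 10.4.3 moves crossover patients to the plasma arm at a fixed day 10 instead of at first infusion, and the adverse-event window is undefined for controls who never receive plasma

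*Protocol*

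**What the plan says.** **Attribution.** Protocol section 10.4.3 sets the principle that "Patients will be evaluated with regard to the treatment actually received". The same sentence then applies it to crossovers by stating that patients who cross "over from the control to the experimental arm will be evaluated in the experimental arm from day 10 onwards".

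**When crossover happens.** Section 6.8 gives the timing as "Starting from day 10 after randomization", with no latest day; section 4 and schedule footnote 1 agree. Eligibility must be checked again, and section 6.8 adds that "The actual possibility for cross-over into the experimental arm is based on discussion with the coordinating investigator on a case-by-case decision". Section 7.1 says that "Cross-Over starts with baseline visit and follows the primary schedule of the study". Candidates are standard-arm patients whose condition has failed to improve or has deteriorated.

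**AE window.** Footnote 26 to the trial schedule says: "Patients must be followed for AEs from first plasma administration up to 28 days after last plasma administration", extended if drug-related toxicity persists. Section 9.2 repeats this window, but also says that every AE after consent is documented and that AEs are collected throughout the trial.

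**Comparison.** The Safety Analysis text in section 10.5.5 reports the number and percentage of patients with AEs. It adds: "Incidence rates are summarized along with two-sided Clopper-Pearson 95% confidence intervals and analyzed by (descriptive) chi-squared tests". It states no adjustment for time observed.

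**The concern.** Day 10 is a lower bound for crossover, but section 10.4.3 uses it as the date of exposure. Between day 10 and the real infusion a crossover patient has had no plasma, yet any AE in that interval is charged to plasma. The rule breaks the as-treated principle it is meant to apply. It does so in a selected group, since only controls who are doing badly qualify.

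The AE window is a second, separate problem. Both places that define it count from plasma administrations. A control who never crosses over has no such dates, so the protocol fixes neither the start nor the end of that patient's AE follow-up. The text on recording from consent supplies a start but no clear end, and it does not fit the plasma-based window beside it. A percentage of patients with at least one AE grows with observation time, so the between-arm comparison is interpretable only if the windows match.

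At stake is the tabulated comparison of AE frequencies for a product whose listed risks in section 6.3 include circulatory overload, lung injury and a theoretical antibody-mediated enhancement.

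**Working it through.** The protocol gives no figure for the size of this problem, so there is nothing to reproduce. The steps below apply its rules literally.

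**1. Plasma-free days counted as plasma (from the text).** Let T be the day after randomisation on which a crossover patient is first infused. Misattributed days = T − 10. The second infusion is on T + 1, so the basic AE window ends on T + 29. Days counted to plasma from day 10 to that end, inclusive = T + 29 − 10 + 1 = T + 20.

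| T | Misattributed days (T − 10) | Days counted (T + 20) | Share |
|---|---|---|---|
| 10 | 0 | 30 | 0% |
| 14 | 4 | 34 | 12% |
| 17 | 7 | 37 | 19% |
| 21 | 11 | 41 | 27% |
| 28 | 18 | 48 | 38% |

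Splitting each patient's time at the actual infusion makes the second column zero throughout.

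**2. How many patients could be affected (upper bound).** Section 10.3 assumes exponential times with a control median of 16 days and 87 patients per arm. Proportion unimproved at day 10 = exp(−ln 2 × 10/16) = 0.648, and 0.648 × 87 ≈ 56. This ignores deaths, the renewed eligibility check and the case-by-case decision, so it is a ceiling and not a forecast.

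**3. Illustration of size (assumed inputs).** The documents give neither the number of crossovers nor their infusion days.
- Assume 9 to 28 crossovers infused on day 14 to 21. Misattributed person-days run from 9 × 4 = 36 to 28 × 11 = 308.
- Plasma-arm person-days in the basic window = 87 × 30 + crossovers × (T + 20). The shares are 36/2916 = 1.2% and 308/3758 = 8.2%.
- Assume also a daily pre-infusion AE probability of 2% to 5%. Crossovers with at least one pre-plasma AE charged to plasma run from 9 × (1 − 0.98⁴) = 0.7 to 28 × (1 − 0.95¹¹) = 12.1.

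**4. Effect of unequal windows (one possible reading, assumed hazards).** For randomised plasma patients the basic window is day 1 to day 2 + 28, about 30 days. If controls were followed for AEs to day 84 and both arms had the same constant hazard, the control percentage = 1 − (1 − p₃₀)^(84/30).

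| Assumed AE proportion at 30 days | Same hazard at 84 days |
|---|---|
| 20% | 47% |
| 30% | 63% |
| 50% | 86% |

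This gap is pure artefact and makes plasma look safer. The day-10 rule would probably work the other way, because it charges pre-infusion AEs of deteriorating controls to plasma. The two effects oppose each other, so the net direction is not known.

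**The case against.** **Day 10 may be shorthand.** The sentence opens with the as-treated principle. The schedule shows a single crossover assessment at day 10, section 8 ends follow-up of crossovers at day 94 (10 + 84), section 10.5.4 speaks of switching at day 10, and footnote 13 restarts visits at first plasma. If every crossover patient were infused on day 10, the error would be zero. This stands as a limit on size. It does not rescue the wording, because sections 4 and 6.8 and footnote 1 allow later crossover and the required steps make it likely.

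**The analysis plan will hold the details.** Section 10.4.3 says so, and table layout, exposure adjustment and handling of patients with time on both treatments belong there. But the protocol itself fixes day 10 and the plasma-based window, so an analysis plan using infusion dates would contradict it.

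**Controls are covered.** Section 9.2 documents all AEs from consent, and footnote 26 calls recording continuous. A reader might infer that AEs in controls go uncollected, or that the arms are certainly observed for different lengths of time. The text supports neither; the defect is conflicting wording about when follow-up ends.

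**Other safeguards exist.** Causality is judged per event (section 9.2.2), transfusion reactions are reported at once (section 9.7), and the monitoring committee meets after 5, 10 and 25 treated patients (section 1.3.1). The between-arm tests are descriptive. This stands, and it lowers the severity.

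**Conclusion.** The point holds at moderate severity. The day-10 rule is wrong as written: it miscounts T − 10 days for each crossover patient and contradicts the principle in its own sentence. The AE window is undefined for never-infused controls and inconsistent with recording from consent, so the compared percentages may rest on unequal windows. The number of misattributed AEs cannot be derived; the ranges for person-days, AEs and window length rest on the assumptions stated with them. The primary analysis and the sample size of 174 do not change.

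Three stronger readings are tempting and are not supported.
- **A large shift in the plasma AE rate from the day-10 rule.** With 26 crossovers and AE rates of 30% and 60% (all assumed), (0.30 × 87 + 0.60 × 26)/113 = 37% instead of 30%. That shift comes from pooling sicker crossovers with randomised plasma patients and would be the same if every AE were dated from the true infusion.
- **Double counting in the chi-squared test.** Nowhere does the protocol say that crossovers enter both columns of one table.
- **An overall bias against plasma.** The window problem can push the other way.

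**What to change.** - **Section 10.4.3:** replace the fixed day 10 with the date and time of the first plasma infusion as the point from which a crossover patient is evaluated in the experimental arm.
- **Section 9.2 and schedule footnote 26:** reconcile the plasma-based window with documentation from consent. State one AE window for the between-arm comparison, starting at randomisation and of equal length in both arms. Control time ends at first plasma infusion. AEs after crossover are tabulated separately, over their own post-infusion window.
- **Sections 8 and 10.5.4 and the schedule:** reconcile the places that treat crossover as happening on day 10 with those that allow it from day 10. This point takes no position on when crossover should be permitted.

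The cost is an amendment to a few sentences, matching text in the analysis plan and one additional safety table. Infusion dates are already recorded, and AEs in controls are already documented from consent. Treatment, sample size and the primary analysis stay as they are.

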## **10.5 Statistical Methods**

### **10.5.1 General Considerations**

The statistical evaluation is carried out under the supervision of the Supervising Statistician. Statistical analysis is based on the International Conference on Harmonization (ICH) Guidelines “Structure and Content of Clinical Study Reports” and “Statistical Principles for Clinical Trials”. All statistical procedures are done according to the current Standard Operating Procedures (SOPs) of the Institute of Medical Biometry and Informatics, University of Heidelberg (IMBI).

All data recorded in the eCRF describing the sample, the efficacy and the safety are analyzed descriptively. Categorical data are presented in contingency tables with frequencies and percentages. Continuous data are summarized with at least the following: missing values, median, quartiles, mean, standard deviation, minimum and maximum.

The detailed methodology for the statistical analysis is described in the statistical analysis plan (SAP), which is finalized before database lock. Statistical analysis is performed using SAS v9.4 or higher.

### **10.5.2 Demographic and other Baseline Characteristics**

Patients’ disposition and reasons for ending the study are presented in frequency distribution tables and individual data listing. Descriptive statistics of the baseline characteristics are generated across all treated patients. Frequency distributions are presented for the categorical variables. Summary statistics and the number of assessed patients are calculated, as appropriate, for the quantitative variables. Individual data is presented in listings.

Categorical baseline characteristics, like sex, concomitant illness at trial initiation, and concomitant treatment maintained, is summarized by frequency tables. Summary statistics such as mean, standard deviation, median, first and third, quartile, as well as minimum and maximum, are provided for quantitative variables like age, weight, laboratory values.

### **10.5.3 Study Therapy, Treatment Compliance, and Follow-up**

Summary statistics are presented for the amount and dosage of CP received, dose modifications for toxicity, discontinuation and withdrawal from study treatment, as well as drop-out from the follow-up.

### **10.5.4 Analysis of the Primary Endpoint**

The primary analysis will assess the null hypothesis “the cumulative improvement curves for the primary endpoint in the experimental and control arm are equal”, i.e.  $H_0: S_E = S_C$  against the alternative hypothesis  $H_1: S_E \neq S_C$  at a two-sided significance level of  $\alpha=5\%$ . This will be achieved by using the log-rank test stratified for the factor “patient group” as used in the randomisation procedure. The event “death from any cause” will be handled by censoring those patients at day 84 (in analogy to the approach of Cao et al, NEJM 2020). Using this approach ensures that deceased patients are considered as “not improved” over the whole observation period of 84 days. The hazard ratio for treatment group will be determined using a Cox regression model stratifying for the factor “patient group” together with a 95% confidence interval. The cumulative improvement curves are calculated using the Kaplan-Meier method together with 95% log-log-type confidence bands, and will be calculated separately for both treatment groups. In addition, cumulative improvement curves will also be calculated separately for each patient group per treatment group.

The fact that some patients from the control group might switch to the experimental group at day 10 will be ignored in the primary analysis, representing a treatment policy approach

according to the ICH E9 (R1) addendum on estimands . Patients who drop out during the trial or are lost to follow-up are taken into account as censored observations. The primary analysis will be based on the FAS according to the ITT principle.

A supplementary analysis of the primary endpoint will involve the inverse probability censoring weighting (IPCW) approach to estimate a treatment effect in the hypothetical scenario that patients from the control group had not switched to the experimental group . This type of model requires to estimate the probability for a patient to switch to the experimental group based on (time-dependent) covariates, which in our case will be the baseline factor “patient group”, together with the time-varying factors “seven point ordinal scale measuring clinical improvement” and “viral load” over time. It should be noted that this model implicitly assumes that all relevant confounders predicting whether a patient switches from control to treatment have been included into the model, an assumption which is hardly verifiable, especially for such a recently emerged disease about which we currently only have limited understanding, thus being the reason why we did not choose this as the strategy for the primary analysis.

As another supplementary analysis intending to estimate the treatment effect in the hypothetical scenario which assumes that control patients had not switched to the treatment group, a rank preserving structural failure time (RPSFT) model will be fitted . This model assumes a common treatment effect, meaning that the treatment effect is the same for all individuals (with respect to time spent on treatment) regardless of when treatment is received. Since this is another assumption which is hardly verifiable, and because we especially assume that patients will have a larger treatment effect when plasma is given early, we consider this approach as a supplementary analysis only.

Further sensitivity analyses of the primary endpoint include an analysis based on the per protocol population.

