### **6.6 Enrolment, Randomisation, Treatment Assignment**

A subject is considered enrolled when he or she has signed the Informed Consent form. The patient receives a screening number at the clinical site (number of site plus number of patient in ascending order, e. g. 001-001 for the first enrolled patient at site 01) via registration in the eCRF system (www.xxx.). The screening number is used to identify the

---

 This section of the study protocol is defined as reference safety information (RSI).

subject throughout the clinical study and must be used on all study documentation related to the subject.

Clinical sites must complete the baseline case report forms for all enrolled subjects, even if the subject is not randomised or treated in this study.

Upon confirmation of eligibility (patients must meet all inclusion criteria and must not meet exclusion criteria), the clinical site must contact a centralized internet randomization system (<https://randomizer.at/>). Patients are randomized using block randomisation to one of the two arms, experimental arm or standard arm, in a 1:1 ratio considering a stratification according to the 4 risk groups (as described in the inclusion criteria).

All subjects randomised receive a unique randomisation number. All patients in the experimental group have to start CP treatment within 7 days of randomization. Patients withdrawn from the trial retain their Patient ID and randomization number.

The study is open-label.

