### **7.3.1 Seven point ordinal scale**

The seven point ordinal scale value is determined at the time of study inclusion and afterwards until discharge within 84 days after randomization or end of trial. This endpoint was also recommended by the WHO R&D Blueprint expert group (Coronavirus disease (COVID-2019) R&D. Geneva: World Health Organization (<https://www.who.int/blueprint/priority-diseases/key-action/novel-coronavirus/en/>)). The seven-category ordinal scale consists of the following categories: 1, not hospitalized with resumption of normal activities; 2, not hospitalized, but unable to resume normal activities; 3, hospitalized, not requiring supplemental oxygen; 4, hospitalized, requiring supplemental oxygen; 5, hospitalized, requiring nasal high-flow oxygen therapy, noninvasive mechanical ventilation, or both; 6, hospitalized, requiring ECMO, invasive mechanical ventilation, or both; and 7, death.

This scale is clearly defined and values will be obtained daily for each patient until day 28, thereafter weekly until day 56, then on day 70 and finally at day 84. A change in two points is clinically meaningful in either direction. For example, a patient with an improvement from #4 (oxygen supplementation, hospitalized) to #2 (discharged, no oxygen) is clearly relevant. Also, a change from #5 (high flow oxygen) to #3 (hospitalized but no supplemental oxygen) is clearly relevant as well. Of note, inclusion criteria of the trial determine that all patients to be included are either in #4 or #5 at time of inclusion into the trial.

Physicians or nurses record the scale value daily at the same time. The time can be fixed individually for each patient. Recordings are obtained +/- one hour of the intended time.

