## 10.3 Sample Size Calculation

Based on recently published data median time to an improvement defined as two points on a seven point ordinal scale or live discharge from the hospital is assumed to be at day 16 from randomization. This median estimate considers patients who died without an improvement as censored at day 84 (right-censoring), which ensures that those patients are considered as “not improved” over the whole observation period. In our trial, we follow the same analysis strategy as in Cao *et al.*, 2020 who also censored deceased patients at the end of follow-up.

We assume that based on the mechanism of action (neutralizing antibodies) a rapid improvement is induced by fresh frozen plasma from subjects after convalescence of SARS-CoV-2 infection on two days from two different donors with a median time of 10 days (HR=1.6). Assuming exponentially distributed event times, these assumptions correspond to a hazard of  $\lambda_C = 0.043$  for the control arm, while the corresponding hazard in the experimental arm should amount to  $\lambda_E = 0.043 \cdot 1.6 = 0.69$ .

While it is allowed for patients from the control arm to switch to the experimental arm starting at day 10 (see section 6.8), we assume this will not have a major effect on the median time of clinical improvement for these patients, since we expect that plasma infusions will have a larger advantage if given early. While methods for handling patients switching from control to treatment group are available, they are subject to strong and unverifiable assumptions. Hence, we will ignore treatment switch in the primary analysis, representing a treatment policy strategy (see Section 10.2.1), which can be regarded as a conservative approach since switching is only allowed from the control to the experimental arm. However, in supplementary analyses of the primary endpoint, we will consider such a hypothetical scenario in which a treatment effect is estimated for the case that patients would not have switched by means of inverse probability censoring weighting according to Robins & Finkelstein, relying on the assumption that there are no unmeasured confounders influencing the probability to switch, and a rank preserving structural failure time (RPSFT) model, assuming a common treatment effect which remains constant over time, regardless when treatment is initiated.

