Since patients might die before experiencing a clinical improvement or being discharged from the hospital, death will be taken into account via censoring deceased patients at last day of follow-up (day 84). Based on recently published data, the mortality rate is assumed to be about 20% in the control arm. Thus, we expect that the cumulative improvement rate of the control group will not become larger than 0.8. Hence, fewer improvement events are expected during the follow-up of 84 days than under the assumption of an exponential distribution, since the improvement curves will flatten at some point. In case of the control group, the flattening is expected to occur at day 38, since the assumed cumulative improvement rate at day 38 amounts to  $\exp(-\lambda_C \cdot 38) = \exp(-0.043 \cdot 38) \approx 0.8$ . Accordingly, we conservatively assume a follow-up length of 38 days for the sample size calculation to properly estimate the probability of experiencing the event of interest, even though the actual follow-up for each patient will be longer.

To detect the assumed difference between treatment groups using a log-rank test comparing the cumulative improvement curves for the primary endpoint using a significance level of 5% (two-sided) with a power of 80%, a total number of 174 patients is required for the entire trial (87 patients per group) when additionally considering a dropout rate of 5%, meaning that n=164 patients who do not prematurely drop out of the study are required to be enrolled. The required number of events which was calculated using the formula by Schoenfeld, amounts to 142. It is expected that adjusting for the covariate “patient group” in the analysis will lead to an increase in power. Sample size calculation was done conservatively assuming an equally long follow-up period of 38 days for every patient. Sample size calculation was done using RPACT v 2.0.6.

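### The primary test and Cox model leave out the baseline ordinal category (4 or 5), which decides what event each patient must reach; this may cost efficiency but not validity

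*Protocol*

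**What the plan says.** - **Primary analysis.** Protocol 10.5.4 and the synopsis (Statistical Analysis) name a log-rank test stratified by patient group. For the effect estimate, 10.5.4 says "The hazard ratio for treatment group will be determined using a Cox regression model stratifying for the factor" patient group. No other factor enters.
- **Randomisation.** Section 6.6 allocates "in a 1:1 ratio considering a stratification according to the 4 risk groups". Baseline category is not a stratum.
- **Baseline category.** Section 7.3.1 has the scale value determined at inclusion and states that "inclusion criteria of the trial determine that all patients to be included are either in #4 or #5". The trial schedule (Table 1) also marks the scale at screening/baseline.
- **Event.** The primary endpoint is a two-point improvement or live discharge, whichever comes first (section 3). The two worked examples in 7.3.1 are 4 to 2 (out of hospital) and 5 to 3 (in hospital without oxygen).
- **Adjustment elsewhere.** Section 10.3 expects adjustment for patient group to raise power. Section 10.5.5 adjusts viral load and antibody titres for their baseline value. The ordinal scale is a covariate only in the supplementary IPCW model for treatment switching (10.5.4).

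**The concern.** Baseline category does more than describe severity. It fixes the target: discharge for a patient starting in category 4, an in-hospital step for a patient starting in category 5. The primary analysis puts both kinds of patient into the same risk sets within each patient group. If event hazards differ by category, leaving the category out pulls the estimated hazard ratio toward 1 and lowers the power of the test. There is little room for this, because the protocol's own simulation gives 0.785 in the base case (Table 3). That simulation gives all controls a single median of 16 days, so it does not examine different control hazards by category.

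**Working it through.** **Inputs from the protocol (10.3).**
- Test: "using a significance level of 5% (two-sided) with a power of 80"%.
- Control median: "is assumed to be at day 16 from randomization".
- Effect: "with a median time of 10 days (HR=1.6").
- Follow-up: "we conservatively assume a follow-up length of 38 days for the sample size calculation".
- Deaths: "the mortality rate is assumed to be about 20% in the control arm", with 13% in the experimental arm in the simulation.
- Size: 164 evaluable patients, in groups of 42, 40, 42 and 40.

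**Inputs assumed, because the protocol does not give them.** Share in category 5: 20-50%. Event-hazard ratio, category 5 versus 4: from 1 down to 0.33, and 2 in the other direction.

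**Step 1: reproduce the plan.**
- Schoenfeld events: 4 × (1.960 + 0.842)² / (ln 1.6)² = 31.40 / 0.2209 = 142.1. The protocol states 142.
- Control hazard: ln 2 / 16 = 0.0433 per day.
- Event probability at 38 days: control 1 − exp(−0.0433 × 38) = 0.807; experimental 1 − exp(−0.0433 × 1.6 × 38) = 0.928; mean 0.868.
- Patients: 142.1 / 0.868 = 163.8, so 164. With 5% dropout, 82 / 0.95 = 86.3, so 87 per arm and 174 in total.
- Simulating the first row of Table 3, with deaths kept as not improved, gives power 0.783 against the stated 0.785.

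The stated design is arithmetically sound.

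**Step 2: let category carry prognosis.** Same set-up, with the overall control median held at 16 days and the hazard ratio at 1.6 within category. There were 2,500 trials per row, so the Monte Carlo standard error is about √(0.77 × 0.23 / 2500) = 0.008. Both columns come from a Cox model stratified by patient group.

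| Share in cat. 5 | Hazard, 5 vs 4 | Power, group only | Power, category as covariate |
|---|---|---|---|
| 35% | 1 | 0.789 | 0.789 |
| 20% | 0.67 | 0.770 | 0.767 |
| 35% | 0.67 | 0.763 | 0.774 |
| 20% | 0.5 | 0.735 | 0.775 |
| 35% | 0.5 | 0.722 | 0.770 |
| 50% | 0.5 | 0.727 | 0.775 |
| 35% | 0.33 | 0.642 | 0.756 |
| 35% | 2 | 0.714 | 0.762 |

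At 35% in category 5 and hazard ratio 0.5, the average estimated treatment hazard ratio is 1.58 without category and 1.63 with it. Type I error is 0.052 either way.

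A further simulation over 20-50% in category 5 (2,000 trials per cell) puts the change from adding the covariate at:
- 0 to −0.5 point if category is not prognostic;
- +0.5 to +1.6 points at a 1.5-fold difference;
- +2.6 to +6 points at twofold;
- +8 to +12 points at threefold.

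**Step 3: the other reading of 1.6.** If 1.6 is the effect without adjustment for category, the within-category effect must be larger. With 35% in category 5 and hazard ratio 0.5, a within-category effect of 1.68 gives power 0.814 for group only and 0.851 with the covariate. The average group-only estimate was then 1.66, slightly above target, so both levels are a little generous. The gain is similar, but the planned test does not fall below 80%.

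**Step 4: crossed strata as an alternative.** Four groups by two categories make 8 strata for 164 patients. With 20% in category 5, each category 5 cell holds about 164 × 0.20 / 4 = 8 patients. If category is not prognostic (8,000 trials per cell; 20, 35 and 50% in category 5), power goes from 0.789, 0.793 and 0.787 to 0.768, 0.765 and 0.764, a loss of 2.1 to 2.8 points. The gain is 1.5-2.6 points at a twofold difference and about 6-9 at threefold.

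**The case against.** The strongest defence is that nothing here is an error. The analysis strata equal the randomisation strata, which is coherent, and which further covariates to add is a design choice. That stands.

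The size of the loss is also open. A category 5 patient may recover more slowly but has the nearer target, so the two effects may partly cancel in the event hazard. Exclusion criterion 4 (section 5.4) bars non-invasive ventilation, so category 5 at entry means high-flow oxygen only, which narrows the contrast with category 4. Both arguments stand, and they are why the gain may be small.

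A reader might infer that chance imbalance in category biases the test. One standard deviation of imbalance, at an even split, is √(0.25 × 2 / 82) = 0.078, or about 8 percentage points. Randomisation already covers this in the type I error, so it costs precision and does not bias the test. Part of the gap between the adjusted and unadjusted hazard ratios is also non-collapsibility: the two estimate different quantities.

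**Conclusion.** The point holds as a loss of efficiency. The protocol fixes a primary test that leaves out a baseline value which is already collected and which defines the patient's event. With an effect of 1.6 within category and 20-50% of patients in category 5, the group-only test has about 79% power if category is not prognostic, 71-76% at a twofold hazard difference and 63-69% at threefold. The covariate form stays at about 75-79%.

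A reader might infer that the trial is underpowered or its primary test invalid. The documents do not support either. Type I error is kept, the sample size reproduces, and the protocol gives neither the category split nor the hazards by category. If 1.6 is read as the unadjusted effect, the planned power is roughly met and the covariate adds to it. All the simulated gains also assume proportional hazards between the two categories.

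**What to change.** In 10.5.4 and the synopsis, prespecify one form with no data-dependent switch. The primary test and hazard ratio come from a Cox model stratified by patient group, with treatment and baseline ordinal category (4 versus 5, last value before randomisation) as covariates. The group-stratified log-rank test stays as a sensitivity analysis. Align the summary measure in 10.2.1, which names the log-rank test. Do the same for time to discharge in 10.5.5; there the event is the same for both categories, so the reason is prognosis alone.

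Do not cross group with category, which costs about 2-3 points if category is not prognostic. Do not add a fallback for sparse cells without a threshold either: in an open-label trial that leaves the primary test to judgement on the data.

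The cost is a few sentences and no new data or patients. Power falls by at most about half a point if category is not prognostic. The reported hazard ratio becomes conditional on baseline category and should be labelled so.
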